**9.** **STATISTICAL ANALYSIS**

## Descriptive statistics

Since nothing is known about cellular immune responses against *B. pertussis* in the Dutch population, data of these responses after the booster vaccination with DTPacv-IPV at 8-9 years as well as in the control group will be presented in descriptive statistics, including frequency tables and charts. Descriptive statistics will mainly constitute measures of central tendency (e.g. mean) and measures of dispersion (e.g. range and standard deviation). Antibody levels against the different pertussis antigens will be described in figures and geometric means will be calculated. Differences between the antibody levels pre- and post vaccination will be analysed with a paired t-test. The cellular responses will also be described in figures. Correlations will be measured between the cellular responses and the antibody levels.

Considering the number of children who are already included in the previous study (60 participants) and the expectation of 15% of the children will quit the study prematurely, we aim for 70 children.

The number of 60 children per age group in the former Memory study, is calculated as follows:

To be able to describe significant differences in serological responses between groups or time-points per group, the size of the study groups is dependent on the number of data available from former studies with the “old” WCV and the observed mean antibody titers against the pertussis vaccine components. Data from the DTPwcv/Hib “mixture” study performed in 1993-1994 (Labadie et al 1996) are available from 90 samples. If we combine these data with results from MMR studies (also pertussis measured) a total of 268 data are available. Inclusion of 45 children in each group in this study would mean that there has to be a 2.3-fold rise in mean antibody titers for antibodies against PT and a 2.0-fold rise in that for PRN between groups (power of 90% and a significant level of 5%) using data from the DTwcP/Hib mixture study only (n=90). If also the other available data (n=268) are included these titer rises would become 2.1-fold for PT and 1.8-fold for PRN needed to detect a significant difference with the same power and level. Recent experiments has clearly indicated that at 28 days after vaccination significant differences in antibody responses were found between groups consisting of 35 children of 4 years, which had received either Triaxis or Infanrix-pertussis as a booster vaccine.

Considering the available time span and the area’s where the study has to be performed it is realistic to aim for 45 children per group. Anticipating withdrawals and dropouts during the trial the objective is to include 60 children per group. This will allow us to observe a statistically significant difference between the different time-points before and after booster vaccination if we measure a twofold rise in the antibody titer against these antigens of the pertussis vaccine component.

For the control group we aim for 20 children who did not receive the extra ACV booster at age 8-9 years and who have the same age as the children under investigation in the study. One bloodsample will be taken one year after the regular DTP vaccination to exclude the effect of *Bordetella pertussis* circulation on the immunological parameters measured. Since pertussis antibody levels wane in 2-3 years after vaccination, high antibody levels will indicate a recent infection with *Bordetella pertussis* in this control group. For comparison of the results of the children who received the extra pertussis vaccination with this control group one-year post-vaccination, we will use an unpaired t-test. Antibody levels and cellular responses will be described in descriptive statistics and figures. In this way, we can improve the understanding of the vaccine effect on the immunological parameters measured.

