# 2. OBJECTIVES

Primary Objective:

To assess the longitudinal kinetics of the long term cellular immunity to *B. pertussis* after ACV and the relationship between the cellular (long term) immunity and antibody responses.

There is little knowledge of the cellular immune response against *B.pertussis* in Dutch children. These data are very relevant to obtain insight in the effect of vaccination on the long term protection against *B. pertussis* as well as the effect of changes in the vaccination program on the immune status of children.

The primary objective of this study is to get insight in the longitudinal kinetics of the B- and T- cellular memory immune responses against *B.pertussis* and the relationship with the antibody response induced after an extra booster vaccination with ACV at 8-9 years of age.

- Memory B- and T- cells will be isolated and after polyclonal stimulation will be tested against various proteins of B. pertussis.
- Antibody responses will be measured against the various proteins of B.pertussis.

Secondary Objective:

If there are enough lymphocytes, the immune response (memory B- and T-cells and antibody responses) to other vaccine preventable diseases, like measles, mumps, diphtheria, tetanus and polio will also be measured.

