**3. Study design**

Interventional study with a single intervention (an extra DTPacv-IPV booster vaccination in the 8-9 years old children) and blood samples taken pre-vaccination and post-vaccination at 28 days and 1 year after the extra booster. The time window for the blood sample at 28 days will be  2 days and the time window for the blood sample 1 year after vaccination will be  2 weeks. A questionnaire will be taken about the clinical symptoms of whooping cough (annex 4).

A control group including children of the same age who did not receive the extra ACV booster at age 8-9 years will be included. One bloodsample will be taken one year after the ‘regular’ DTP vaccination.

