## Sample size calculation

This study is designed to investigate the direct as well as the long term effect of the acellular pertussis vaccine on the cellular immunity by measuring the cellular immune responses and the antibody titers after primary series and an extra booster vaccination.

Data on cellular immune responses against *B. pertussis* in Dutch children are not yet available.

An ongoing study that compares the effect of WCV and ACV on the long term cellular memory immunity against *B. pertussis* and the other components of the DTP-IPV-Hib vaccine in Dutch children, started in 2006 and aims for 60 children per age group. To compare these data with the data that will be attained in this study, we aim for a total of 60 children. However, we expect about 15% of the children to stop prematurely; therefore we aim for a total of 70 children.

For a control group we aim for 20 children. A group of 20 children of 10 years of age not being boostered with a pertussis vaccine at 9 years of age will be included in the study. If circulation of pertussis will be increased during the last year, the geomean antibody titers against pertussis toxin (PT) will be increased in our control group in 2010 compared to 9 years old children before booster vaccination in 2009. Moreover, in addition to PT antibody titers the percentage of PT specific memory B-cell responses will increase too due to a higher circulation of pertussis (Buisman et al, Vaccine 2009). However, a high increase in the circulation of pertussis is very unlikely.

Our previous studies in 2007 showed equal geometric mean antibody titres in children of 6 to 10 years of age, in groups of 60 children as well as in groups of 20 children. Therefore, the number of 20 children in this control group will be sufficient to calculate any effect of recent circulation of pertussis on pertussi toxin specific antibody titers or memory B-cell responses.

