# 5 TREATMENT OF SUBJECTS

## 5.1 Investigational treatment

#### Children of 8-9 years old will be asked to receive an extra pertussis-component in the DT-IPV booster vaccination (DT*Pacv*-IPV) together with their MMR vaccination. There will be no extra injection, only a change in vaccination composition (addition of the pertussis component). Pre- and post-vaccination a blood sample of 15 ml will be taken by venous puncture. Post-vaccination blood sampling will be done at 28 days (± 2 days) and 1 year (± 2 weeks) after the booster vaccination. To examine *B. pertussis* specific memory B- and T-cells we need a minimum of 1 x 106 Peripheral Blood Mononuclear Cells (PBMC's) to analyse one of the 5 most important *B. pertussis* specific antigens (Ptx, Prn, FHA, Fim 2 and 3). B- cells account for only 2 to 10% of all PBMC's and only 20-30% of all B- cells are memory B- cells. On average we can isolate 1 x 106 PBMC's per ml blood, however this is highly variable per person. To analyse specific memory B- cells to all 5 *B. pertussis* antigens, an amount of 15 ml blood is needed. With less material, B- cell responses against just one or two proteins of *B. pertussis* (Ptx, Prn or FHA) will be measured. In our ongoing study a blood sample of 15 ml is not a problem in 8-9 years old children.

##

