# METHODS

## 7.1 Study parameters/endpoints

#### 7.1.1 Main study parameter/endpoint

The main study parameters will be the longitudinal kinetics of B- and T- cell memory immune responses and antibody responses against the vaccine proteins of *B. pertussis*.

Blood samples will be separated in Peripheral Blood Mononuclear Cells (PBMC's) and plasma samples. PBMC's will be divided in purified B- cell populations and T- cell populations.

B- cells will be cultured and memory B- cells will be polyclonal stimulated (Bernasconi et al, 2002). After 5 days stimulation, B- cell memory responses will be measured against the various proteins of *B. pertussis* (FHA, pertactin, PT, Fim 2 and 3) by ELIspot assays and MIA (Multiplex Immuno Assay) or ELISA of the culture supernatants.

The plasma samples will be used to measure antibody responses against the various proteins of

*B. pertussis* (PT, PRN, FHA, Fim 2 and 3), and, if necessary to the extra components of the National Immunization Program. IgG and IgA antibody titer is measured in

multiplex immuno assay (MIA) (Gageldonk et al 2008) in two dilutions using FDA reference

serum as standard (EU/ml, Meade et al 1995).

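### Kinetics of cellular memory are a primary aim, but the pre/post paired analysis is given to antibodies only: no within-child cellular change is estimated, and the sizing is serological

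*Protocol*

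**What the plan says.** **Aim.** Section 2 opens the primary objective with "To assess the longitudinal kinetics of the long term cellular immunity to" *B. pertussis* after the booster, and adds the relationship between that immunity and the antibody responses. Section 7.1.1 agrees: "The main study parameters will be the longitudinal kinetics of B- and T- cell memory immune responses and antibody responses against the vaccine proteins of" that organism.

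**Data.** Section 3 provides for "blood samples taken pre-vaccination and post-vaccination at 28 days and 1 year after the extra booster". Controls give one sample, a year after their routine vaccination.

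**Analysis.** Section 9.1 says that cellular data in boosted children and controls "will be presented in descriptive statistics, including frequency tables and charts", with means, ranges and SDs. The reason given is that these responses are unknown in the Dutch population. The pre/post comparison by paired t-test is then named for antibody levels. The next sentence on the cells reads "The cellular responses will also be described in figures". Correlations between cells and antibodies follow, and Section 9.2 assigns them a Spearman test. Later in Section 9.1, the boosted children's results at one year are compared with the controls by unpaired t-test, without naming the variables; antibodies and cells are then both said to be described.

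**Sizing.** Section 4.4 takes 60 children to match an ongoing study and enrols 70 to allow for dropout. Section 9.1 explains where the 60 came from: "To be able to describe significant differences in serological responses between groups or time-points per group".

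**The concern.** Kinetics means change over time within the same child. The design pays for it with three venous samples from each boosted child, yet the one analysis that uses the pairing is written for antibodies. Followed as written, the plan would report cellular levels visit by visit and their correlation with antibodies, but not how much a child's memory response changed by day 28 or by one year, nor how precisely that change is known.

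This is more than detail left to a statistical analysis plan. The protocol is not silent: it allocates the paired test to one class of outcome and description to the other. A later plan that added a paired cellular analysis would be going beyond the protocol's own allocation.

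**Working it through.** **1. Objective against analysis**

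| Part of the main aim | Data collected | Analysis named |
|---|---|---|
| Antibody kinetics | 3 samples per child | Geometric means, figures, paired t-test |
| Cellular kinetics | 3 samples per child | Tables, mean, SD, range, figures |
| Cells v antibodies | Same samples | Correlation, Spearman test |
| Boosted v control at 1 year | 1 sample per control | Unpaired t-test (variables not named) |

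Only the second row lacks an analysis of change.

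**2. Can the named analyses stand in for it?**

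- *Visit summaries.* If the same n children are measured at both visits, the difference of two visit means equals the mean change. Its variance, with equal SDs σ at the two visits, is 2σ²(1 − ρ)/n, where ρ is the within-child correlation. Means and SDs per visit do not reveal ρ, so the standard error cannot be recovered. For illustration, if ρ lies between 0 and 0.5, the true standard error is between 1 and √(1 − 0.5) = 0.71 times the value obtained by treating the visits as independent. With dropout, the visit means also rest on different children.
- *Spearman correlation.* This addresses association between two measures, not change over time.
- *Unpaired test against controls.* Even if it includes cells, controls have no pre-vaccination sample. It compares levels at one time.

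**3. The plan's own sizing**

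- Enrolment: 60/(1 − 0.15) = 70.6, so 71; the stated 70 leaves 70 × 0.85 = 59.5 completers. This reproduces within rounding.
- Fold rises: 90% power at 5% (two-sided assumed), 45 children against 90 or 268 earlier samples. No SD is stated, so it is back-calculated: SD = log10(fold) / [(1.960 + 1.282) × √(1/45 + 1/n₂)].
  - n₂ = 90: PT 0.3617/0.5918 = 0.611; PRN 0.3010/0.5918 = 0.509.
  - n₂ = 268: PT 0.3222/0.5222 = 0.617; PRN 0.2553/0.5222 = 0.489.
- Applying the n₂ = 90 SDs at n₂ = 268 predicts 10^(0.6112 × 0.5222) = 2.09-fold for PT and 10^(0.5087 × 0.5222) = 1.84-fold for PRN, against 2.1 and 1.8 stated. The figures are mutually consistent.

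All of these inputs are antibody titres, as is the twofold rise quoted for comparisons between time points. There is no cellular sizing figure to reproduce.

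**4. What the collected pairs could show**

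The smallest detectable mean change, in SDs of the within-child differences, is approximately (z₀.₉₇₅ + z_power)/√n:

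- n = 60: 3.2415/√60 = 0.418 (90% power) and 2.8016/√60 = 0.362 (80%). The exact noncentral-t values are 0.425 and 0.368.
- n = 45, as an example of fewer evaluable pairs: exact values 0.494 and 0.427.

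The half-width of a 95% confidence interval is t/√n: 2.001/√60 = 0.26 SD for 60 pairs and 2.015/√45 = 0.30 SD for 45.

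**The case against.** The strongest defence is that this is a descriptive study. Section 2 seeks insight and sets no hypothesis that cells are higher at one year. Section 9.1 gives a reason for description, and half of the primary objective, the relationship with antibodies, has a named test. That stands as far as hypothesis testing goes: no p-value is required. It does not cover estimation. A descriptive study of kinetics should still report the size of the change and its uncertainty, and lack of earlier data excuses the missing power calculation, not the missing estimate.

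Four stronger readings are tempting and are not supported:

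- *That cellular data are only plotted, or get no inferential analysis.* They also get tables, means, SDs, ranges and a tested correlation, and perhaps the one-year comparison with controls.
- *That the stated lack of cellular data contradicts Section 4.4.* That section expects that "the percentage of PT specific memory B-cell responses will increase too due to a higher circulation of pertussis", citing a publication, and mentions an ongoing cellular study. But it also says that cellular data in Dutch children are not yet available, which agrees with Section 9.1. The content of the cited paper cannot be judged from the protocol.
- *That pairs will be lost because different antigens are assayed at different visits.* Section 5.1 says "With less material, B- cell responses against just one or two proteins of" *B. pertussis* will be measured, and gives no order among PT, PRN and FHA. Switching is therefore possible, but it is neither stated nor quantified. Average yield is 15 ml × 10⁶ = 15 × 10⁶ cells against a minimum of 5 × 10⁶ for five antigens, about threefold, although yield is said to vary widely. Laboratory procedures may already fix an order.
- *That the trial is too small for cellular outcomes.* Without a cellular SD, neither adequacy nor inadequacy can be shown.

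**Conclusion.** The point holds in a limited form. For cellular responses, which belong to the primary objective and the main study parameters, the plan specifies no within-child change and no measure of its precision. The paired analysis and all the sizing figures concern antibodies. The gap affects one analysis, not the design: the three samples are already planned.

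With 60 complete pairs the unused comparison could detect about 0.43 SD of the differences at 90% power (0.37 SD at 80%), or give an interval of about ±0.26 SD. These figures assume a two-sided 5% level, roughly normal differences (possibly after a log transformation) and evaluable cells at both visits in all 60 children. With 45 pairs they become 0.49 SD, 0.43 SD and ±0.30 SD. They are generic results for those sample sizes and cannot be expressed as cell frequencies. The choice of a single lead antigen or time point is a matter of preference and is not part of this point.

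**What to change.** In Section 9.1, extend the paired analysis to B- and T-cell memory responses. For each antigen, report the within-child change from pre-vaccination to day 28 and to one year with a 95% confidence interval. Work either on a log scale (with a stated rule for zeros), or by Wilcoxon signed-rank with an interval for the median change. State the number of pairs behind each estimate. Say whether the one-year unpaired comparison with controls includes cellular responses. Add one sentence to Sections 4.4 and 9.1 saying that the sample size was justified on antibody titres only.

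Optionally, state one antigen priority order, the same at every visit, for samples with too few cells, or refer to the laboratory procedure that fixes it. This preserves pairs; the small downside is fewer results for the lower-priority antigens.

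The cost is a few sentences and a few extra analyses of data already planned, with no additional children, visits or blood.

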## Univariate analysis

The significance of correlations will be analysed by the nonparametric Spearman test.

## Multivariate analysis

The data from the questionnaires will be related to the cellular and serological responses measured.

# ETHICAL CONSIDERATIONS

## Regulation statement

This clinical study will be performed according to the current rules for Good Clinical Practice (GCP), as described by the Committee for Proprietory Medical Products (CPMP) of the European Union and the International Committee on Harmonisation (ICH) in "Note for Guidance on Good Clinical Practice, document CPMP/ICH/135/95”, effective since January 17th 1997 and according to the Dutch Medical Research Involving Human Subjects Act (WMO), under the general ruling of the Clinical Trial Directive of the EU (2001/20/EU). These rules include the ethical guidelines described in the "Declaration of Helsinki" (World Medical Association Declaration of Helsinki, Recommendations guiding physicians in biomedical research involving human subjects. Adopted by the 18th World Medical Assembly (WMA), Helsinki, Finland, 1964; amended by the 29th WMA, Tokyo, Japan, 1975; 35th WMA, Venice, Italy, 1983; 41st WMA, Hong Kong, 1989, the 48th General Assembly, Sommerset West, Republic of South Africa, 1996 and the 52nd General Assembly, Edinburgh, Scotland, 2000).

The principal clinical investigator will maintain the privacy of the participant and will be responsible for the welfare of the participant. An experienced physician together with a nurse will perform the vaccination and the blood samplings.

The study proposal will be submitted to the CCMO for review and approval of the clinical investigation and the methods and materials used to gather and register the declaration of informed consent of the participants. Both parents have to sign the informed consent to let their child participate in the study. The study will not start before written approval of the CCMO has been obtained.

Protocol modifications in the ongoing study which affect the safety of the participant, or which alter the scope of the investigation, the scientific quality of the study, the experimental design, assessment variables, the number of participants or the selection criteria, will be made only after appropriate consultation with the Clinical Trial Monitor, the Sponsor/investigator, and the Principal Clinical Investigator.

The CCMO and the BI will be informed of any protocol modification and of severe or unexpected unwanted events that occur during the study and that may adversely affect the safety of the participants or which alter the scope of the investigation, the scientific quality of the study, the experimental design, the number of participants or the selection criteria and the performance of the investigation.

Changes in the protocol will only be made by written amendment agreed upon between the Clinical Trial Monitor, the Sponsor/investigator, and the Principal Clinical Investigator. The amended protocol will not be implemented before approval of the CCMO.

It is the responsibility of the Principal Clinical Investigator to adequately explain the volunteer the aims, methods, anticipated benefits (for participants and/or others), potential discomforts of the study and treatments, both in words and by written information. They will also have the possibility to contact medical doctors for additional information (annexes 2 and 3).

Furthermore, the principal clinical investigator should specifically inform the participant:

- That the privacy of the participant will be maintained by coding the identity. The informed consent implies that participant grants leave to inspect the personal information registered during the study; with access explicitly only to members of the Clinical Research Unit, to the Clinical Trial Monitor, the Medical Ethics Committee and by a qualified authority in case of an audit. The registered information will be archived during a period of 15 years.
- That he/she is completely free to refuse to enter the study at any time, without giving a reason and without consequences for treatment in the event that problems arise.
- On procedures for compensation entitlement in the event of health damage or disablement due to study participation.
- About all relevant information available during the study.

